#### **9.5.4.1 Missing data**

If the probability of missing immunogenicity measurements depends on either covariates or on the immunogenicity outcomes of participants, then the methods described above may give biased inferences and point estimates. If a substantial amount of immunogenicity data is missing (at least 1 value missing from more than 20% of participants), then secondary analyses of the immunogenicity endpoints will be conducted using methods that relax the missing completely at random assumption to a missing at random assumption. For a univariate binary and quantitative outcome, respectively, a generalized linear model with a binomial or normal error distribution will be used for estimation and testing. For assessing repeated immunogenicity measurements, linear mixed effects models will be used. The models will be fit using maximum likelihood methods, and will include as covariates all available baseline predictors of the missing outcomes. The longitudinal models will also include all observed immunogenicity data.

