### 9.5.4 Immunogenicity analysis

The statistical analysis for immunogenicity will employ the intent-to-treat principle, i.e., all data from enrolled participants will be used according to the initial randomization assignment regardless of how many injections they received. The only exception will be to exclude data from HIV-infected participants at or post infection. Thus, for HIV-infected participants, only immunogenicity data from samples known to be drawn prior to HIV infection will be included in the analysis.

If assay data are qualitative (i.e., positive or negative) then analyses will be performed by tabulating the frequency of positive response for each assay by vaccine regimen at each time point that an assessment is performed. Binomial response rates will be presented with their corresponding exact 95% confidence interval estimates. For Parts A and B, crude rates for each vaccine group will be calculated. The combined placebo groups of Part B (N=18) will be used to estimate the false positive rate. Although, because of the lack of precision in this estimate, net response rates will not be calculated for the vaccine groups.

To compare the response rates of any two vaccine arms, a significant difference will be declared if the 2-sided 95% confidence interval for the difference in response rates between 2 groups excludes 0. In addition to reporting the point prevalence response rates, cumulative and cumulative repeat (over time/visit) probabilities of cellular immune responses will be estimated with corresponding confidence intervals using maximum likelihood based methods [102]. Missing responses will be assumed to be missing at random, i.e., conditional on the observed data the missingness is independent of the unobserved responses.

For continuous assay variables, overall differences between groups at a specific time point will be tested by a 2-sample t-test if the data appear to be normally distributed, or by utilizing the nonparametric Wilcoxon rank sum test if the data are not normally distributed. If a portion of the measurements are censored below the assay quantification limit, then the Gehan-Wilcoxon test will be employed. More sophisticated analyses employing repeated

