measures methodology (for example, repeated measures ANOVA or generalized estimating equations) may be utilized to incorporate immune responses over several time points. However, inference from such analyses would be limited by the small sample size of this study. All statistical tests will be 2-sided and will be considered statistically significant if  $p \leq 0.05$ . Graphical descriptions of the longitudinal immune responses will also be given.

Some immunologic assays have underlying continuous or count-type readout that is often dichotomized into responder/nonresponder categories. For these assays, graphical and tabular summaries of the underlying distributions will be made. These summaries may be performed on transformed data (e.g., log transformation) to better satisfy assumptions of symmetry and homoscedasticity. If group comparisons in these underlying distributions reveal that differences are best summarized as a shift in the location of the distribution, then results will be presented in the form of group means (or medians) with associated confidence intervals and statistical tests for differences between groups as described above. If group comparisons in these underlying distributions reveal that differences are best summarized by a mixture model (i.e., responder and nonresponder subgroups are clearly identifiable) then results will be presented in the form of response rates with associated confidence intervals and statistical tests as described above.

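### The missing-data section names only linear mixed models for repeated immunogenicity measurements, which do not suit repeated responder calls or values below the quantification limit

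*Protocol*

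**What the plan says.** Section 9.5.4.1 sets a secondary analysis of the immunogenicity endpoints. It is run when missing data are substantial, meaning "at least 1 value missing from more than 20% of participants". Its purpose is to "relax the missing completely at random assumption to a missing at random assumption". For a univariate outcome, binary or quantitative, "a generalized linear model with a binomial or normal error distribution will be used for estimation and testing". For repeated data there is one instruction: "For assessing repeated immunogenicity measurements, linear mixed effects models will be used". The section adds that the models are fitted by maximum likelihood with baseline predictors of missingness as covariates, and that the longitudinal models also use all observed immunogenicity data.

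The main analysis in section 9.5.4 treats each data type separately:

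- For positive/negative results: "Binomial response rates will be presented with their corresponding exact 95% confidence interval estimates".
- For response over several visits: "cumulative and cumulative repeat (over time/visit) probabilities of cellular immune responses will be estimated with corresponding confidence intervals using maximum likelihood based methods".
- For quantitative results: "If a portion of the measurements are censored below the assay quantification limit, then the Gehan-Wilcoxon test will be employed".
- On the readouts themselves: "Some immunologic assays have underlying continuous or count-type readout that is often dichotomized into responder/nonresponder categories".

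**The concern.** Section 9.5.4.1 makes the binary/quantitative distinction for a single time point and drops it in the next sentence. Because only the longitudinal models use all observed immunogenicity data, an analyst who wants a response rate that draws on other visits under missing at random is led to a normal-error model for a yes/no outcome. The section is also silent on how values below the quantification limit enter that model.

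This analysis exists to support the immunogenicity results when data are missing, and a likelihood-based analysis under missing at random is only as good as its outcome model. At stake are misleading intervals for response rates and a biased between-arm difference in magnitude, in the one analysis meant to protect against missingness.

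**Working it through.** **1. The plan's own figure.** Table 9-2 gives exact 95% intervals at n = 30. With x responders, the Clopper-Pearson limits are the 0.025 quantile of Beta(x, n − x + 1) and the 0.975 quantile of Beta(x + 1, n − x). For x = 15, 18, 21, 24 and 27 this gives [31, 69], [41, 77], [51, 85], [61, 92] and [73, 98], which matches the table. Exact intervals are therefore the benchmark below.

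**2. The text side by side.**

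| Data type | 9.5.4 (main) | 9.5.4.1, one time point | 9.5.4.1, repeated |
|---|---|---|---|
| Responder call | Exact binomial; maximum likelihood for cumulative probabilities | Binomial model | Linear mixed model |
| Value below the limit | Gehan-Wilcoxon | Normal model | Linear mixed model |
| Uncensored quantitative | t-test or Wilcoxon | Normal model | Linear mixed model |

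Only the last row has a repeated-data method that fits the data.

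**3. Mechanism for binary data.** The variance of a binary outcome is p(1 − p), so it changes with the rate, whereas a standard linear mixed model uses one residual variance. As a single-visit illustration, take assumed true rates of 5% and 40%, 30 per arm:

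- Variances: 0.05 × 0.95 = 0.0475 and 0.40 × 0.60 = 0.24; their mean is 0.14375.
- Common half-width: 1.96 × √(0.14375/30) = 0.136.
- Half-width from the 40% arm's own variance: 1.96 × √(0.24/30) = 0.175.
- At an observed 5%, the lower limit is 0.05 − 0.136 = −0.086.

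With the pooled variance, the nominal 95% interval covers 85.7% in the 40% arm, and the 5% arm's lower limit is negative in 98.4% of trials.

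**4. Fitted mixed models.** Inputs from the protocol: 3 groups of 30 vaccinees and nominal 95% intervals. Assumed: 3 visits, latent correlation 0.5, 20% of values after the first visit missing at random, and the response rates. Model: random intercept, group-by-visit means, maximum likelihood, Wald intervals; 200 to 400 runs per scenario.

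| True rate | Linear mixed model, 2% baseline included | Linear mixed model, post-vaccination visits only | Exact binomial |
|---|---|---|---|
| 20% to 70% | 74% to 89% | 84% to 97% | about 95% to 100% |
| 10% or less, or 90% | 90% to 100% | 98% to 100% | about 95% to 100% |

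At true rates of 10% or 90%, 55% to 91% of the linear-model intervals pass 0 or 1. In the scenario with post-vaccination rates of 10%, 30% and 50%, the linear-model width is about 0.27 for all three arms, against exact widths of about 0.26, 0.38 and 0.41. A separate fit of that scenario gave 81% to 87% coverage at 30% to 50%, and 88% for the difference between the 10% and 50% arms. With 200 runs, the simulation standard error at 83% is √(0.83 × 0.17/200) = 0.027, so small differences within these ranges carry no weight.

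**5. Censored magnitudes.** Assume log10 responses with SD σ = 0.6 and a true difference of 0.5. For limit c, substituted value s and a = (c − μ)/σ, the mean after substitution is s·Φ(a) + μ(1 − Φ(a)) + σφ(a). With 40% censored in the lower group, c = 0.6 × (−0.2533) = −0.152, and 13.9% of the higher group is censored. Setting s = c gives means of 0.171 and 0.542. The difference is 0.371, and 0.371/0.5 = 0.74. Substituting the limit divided by d adds log10(d) × (0.400 − 0.139) to the difference; for d = 10 this gives (0.371 + 0.261)/0.5, about 1.27.

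| Censored in lower group | Limit | Limit/2 | Limit/10 | Limit/50 |
|---|---|---|---|---|
| 20% | 0.89 | 0.98 | 1.20 | 1.41 |
| 40% | 0.74 | 0.90 | 1.27 | 1.63 |
| 60% | 0.56 | 0.76 | 1.20 | 1.65 |
| 80% | 0.34 | 0.52 | 0.93 | 1.35 |

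Entries are estimated difference divided by true difference. The bias can run either way.

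**6. Reaching the trigger.** If values go missing independently with probability m, the share of participants missing at least one of k values is 1 − (1 − m)^k. This passes 20% when m exceeds 1 − 0.8^(1/4) = 5.4% for four values, or 1 − 0.8^(1/2) = 10.6% for two.

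**The case against.** The case for leaving the sentence alone has real content.

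- **The readouts are quantitative.** Section 8.7 reports ELISpot as spot-forming cells per million and ICS as percentages of T cells. A linear mixed model is a standard choice for such values, possibly on the log scale. This stands: a reader might infer that all repeated data are binary or censored, but section 9.5.4 has a continuous branch and its censoring clause is conditional.
- **Repeated data may be few.** Sections 8.7.2 and 8.7.3 run the assays at baseline and two weeks after the last vaccination, with other visits only if responses are seen. Responder status at the primary visit alone falls under the binomial model. This limits the reach. It does not remove the problem, because Appendix C draws ELISpot and ICS blood at four Part B visits.
- **Other methods are named.** The maximum likelihood method in 9.5.4 gives cumulative and cumulative-repeat probabilities, not the response rate at a given visit. Generalized estimating equations are optional there and are not the named missing-data method. Gehan-Wilcoxon is a test in the main analysis and does not carry over to a repeated-measures model.
- **Differences fare better than arm rates.** In the single-visit illustration, coverage for the between-arm difference is 93.6%, and in similar simplified settings about 90% to 98%. This stands, although the fitted mixed model gave 88% for 10% against 50%.
- **An SAP can add detail.** It can, but the protocol sentence already fixes the linear model.

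A reader might also infer that the linear model necessarily dilutes an adjuvant or booster effect on magnitude. The documents do not support that. Attenuation follows if censored values are set at or near the limit, but the protocol states no substitution, and lower substitutes mostly inflate the difference.

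**Conclusion.** The point holds in a limited form and is minor. For repeated responder status, the only model named gives arm-level intervals that are clearly too narrow at mid-range rates and often impossible near the extremes. For censored magnitudes it gives a bias of unstated direction. The coverage figures rest on assumed response rates, correlation, missingness and a single residual variance; the censoring ratios rest on an assumed SD, difference and censoring share. The protocol gives none of these, so they show a plausible range and are not predictions.

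It would be wrong to read this as a flaw in the main immunogenicity results. The exact binomial intervals are unaffected. The analysis in question is secondary, depends on the 20% trigger, and matters most if visits beyond baseline and the primary time point are assayed. Section 9.4.2 also says that formal immunogenicity comparisons were not listed as objectives.

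**What to change.** Replace the sentence on repeated measurements in section 9.5.4.1 with three branches:

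- **Repeated responder status:** a binomial-likelihood longitudinal model, for example a logistic mixed model, with a named fallback (such as a penalised fit) if it does not converge at low response rates. Arm-level rates should be averaged over the random effects, because the coefficients are conditional on the participant.
- **Magnitudes with values below the quantification limit:** a mixed model with a left-censored likelihood on the log scale, so that no substituted value is needed.
- **Uncensored, suitably transformed quantitative readouts:** the linear mixed model as now.

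This extends to repeated data the distinction the section already makes for a single time point. The cost is a few sentences and modest programming. The main drawback is possible non-convergence of the logistic model when responses are rare, which is why the fallback should be named in advance.

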#### **9.5.5 Social impact analysis**

Social impacts will be tabulated by type of event and impact on quality of life. The number and percentage of participants experiencing each type of social impact will also be tabulated by impact on quality of life. For this calculation multiple events of the same type for a participant will be counted once under the maximum impact for all post-vaccination visits.

In addition, a listing will be generated of all participants who experienced a major disturbance of their quality of life due to study participation. The listing includes all social impacts experienced by these participants, descriptions of each impact, duration, impact on quality of life, actions taken by the participant and staff, and whether or not there was a resolution.

#### **9.5.6 Analyses prior to end of study**

##### *Safety*

Unblinded interim analyses of safety data are prepared at regular intervals for the HVTN Safety Monitoring Board (SMB). Ad hoc interim safety reports may also be prepared for SMB review at the request of the Protocol Safety Review Team.

*Immunogenicity*

Unblinded immunogenicity analyses will be done only when primary immunogenicity endpoint assay results are available for all samples at the primary immunogenicity time point. Unblinded reports will be provided to the protocol chairs, vaccine developer, other key HVTN members and investigators for the purpose of informing future trial-related decisions after review by the Laboratory Program. Any exceptions must be approved by the SDMC Director and Lab Program Director.

**9.6 Randomization of treatment assignments**

The randomization sequence will be obtained by computer-generated random numbers and provided to each HVTU by the SDMC using the procedures described in the HVTN MOP (Study Operations>Enrollment>Randomization). At each institution, the pharmacist with primary responsibility for drug dispensing is charged with maintaining security of the randomization list. The randomization will be done in blocks to ensure balance across groups.

This page is intentionally blank

# **STUDY OPERATIONS**

## 10 Protocol conduct

The protocol will be conducted according to standard HVTN policies and procedures specified in the HVTN MOP (Study Operations), including procedures for the following:

- Protocol registration, activation and implementation
- Informed consent, screening, enrollment
- Clinical and safety assessments
- Safety monitoring and reporting
- Data collection and documentation
- Study follow-up and close-out
- Unblinding of staff and participants
- Quality control
- Protocol monitoring and compliance
- Advocacy and assistance through local and governmental activities to participants regarding social harms associated with the vaccine trial
- Risk reduction counseling
- Outside testing and belief questionnaire

Any policies or procedures that vary from HVTN standards or require additional instructions will be described in the *HVTN 060 Study Specific Procedures* (e.g., instructions for randomization specific to this study).

## 11 Informed consent

Informed consent is the essential process of ensuring that participants fully understand what will and may happen to them while participating in a research study. The HVTN informed consent form documents that a participant (1) understands the potential risks, benefits, and alternatives to participation, and (2) is willing to participate in an HVTN study. Informed consent is not confined to the signing of the consent form; it also includes all written or verbal study information HVTU staff discuss with the participant, before and during the trial. HVTU staff will obtain informed consent of participants according to the HVTN policies and procedures specified in the HVTN MOP (Study Operations>Informed Consent).

An HVTU may employ recruitment efforts prior to the participant consenting. Some HVTUs use a telephone script to pre-screen people before they come to the clinic for a full screening visit. Participants must sign a screening or protocol-specific consent before any procedures to determine eligibility are performed. HVTUs must submit recruitment and pre-screening materials to IRBs/IECs for human subjects review.

### 11.1 Screening consent form

Some HVTUs have approval from their local Institutional Review Board (IRB) and/or Independent Ethics Committee (IEC) to use a general screening consent form that allows screening for an unspecified HIV vaccine trial. In this way, HVTU staff can continually screen potential participants, and when needed, proceed quickly to obtain protocol-specific enrollment consent. Sites conducting IRB/IEC-approved general screening or pre-screening may use the results from this screening for determining eligibility in this protocol, provided the tests are conducted within the time period specified in the eligibility criteria.

### 11.2 Protocol-specific consent form

The protocol-specific consent form describes the study products to be used and all aspects of protocol participation, including screening and enrollment procedures. A sample protocol-specific consent form is located in Appendix A.

Each HVTU is responsible for developing a protocol-specific consent form for local use, based on the sample protocol-specific consent form in Appendix A. The consent form must be developed in accordance with local IRB/IEC requirements and the principles of informed consent as described in Title 45, Code of Federal Regulations (CFR) Part 46 and Title 21 CFR, Part 50, and in the International Conference on Harmonisation (ICH) Guideline 4.8.10. It must be approved by all responsible ethical review bodies before any participants are consented for the study.

The sample form in Appendix A includes interspersed instructions for developing specific content.

### 11.3 Assessment of understanding

Study staff will ensure that participants fully understand the study before enrolling them. This involves reviewing the informed consent form with the participant, allowing time to reflect on the procedures and issues presented, and answering all questions completely.

An Assessment of Understanding is used to document the participant's understanding of key concepts in an HIV vaccine trial.

When the Assessment of Understanding is used to document the participant's full understanding before the enrollment consent is signed, most IRBs/IECs will require that the participant have been told about the assessment and signed a screening consent. This is because a site may not initiate study procedures without the participant's consent, and administering the Assessment of Understanding can be viewed as a study procedure. The consent process (including the use of the Assessment of Understanding) should be explained thoroughly to the IRB/IEC, whose recommendations should be followed.

The participant must complete the Assessment of Understanding—with assistance of staff, if necessary, in reading and understanding the questions and responses—before first vaccination. Participants should verbalize understanding of all questions answered incorrectly. This process, and the participant's understanding of the key concepts, should be documented in source documentation at the site.

Informed consent does not end with the signing of the consent form. Periodically throughout the study, key study concepts should be reviewed with the participant. At each study visit, HVTU staff should consider reviewing the procedures and requirements for that visit and for the remaining visits.

## 12 Procedures

Participants are considered to be enrolled only upon receipt of the first study vaccination at Day 0.

HVTU and HVTN Laboratory Program staff will conduct pre-enrollment and post-enrollment study procedures according to HVTN procedures as specified in the HVTN MOP (Study Operations). Any procedures which vary from the HVTN standard will be defined in the *HVTN 060 Study Specific Procedures*.

Pre-enrollment and post-enrollment procedures are performed on all participants (unless otherwise noted) at the time points indicated in Appendix B, Appendix C, and Appendix D, using the blood draw volumes specified.

### 12.1 Pre-enrollment procedures

Screening assessments and other pre-enrollment procedures are listed in Table 12-1. Timepoints are specified in Appendix D.

Screening procedures are done to determine eligibility and to provide a baseline for comparison of safety data. Screening may occur over the course of several contacts/visits up to and including Day 0 before vaccination. All inclusion and exclusion criteria must be assessed within 56 days before enrollment, unless otherwise specified in Section 7.

The time interval between randomization and enrollment should not exceed 4 working days, as defined in the HVTN MOP (Study Operations). Subsequently, the HVTU registers the participant by scheduling the Day 0 visit (enrollment) via the web-based randomization system, and requests the randomization assignment.

